### Emergency unblinding

In the event of a severe adverse event occurring in a participant, research personnel must immediately inform the principal investigator to assess and confirm the situation. If emergency unblinding is deemed necessary, the intervention research personnel must promptly notify the research coordinator. The research coordinator will then access the participant's group allocation and specific intervention details to facilitate the emergency unblinding process. Upon unblinding, the research coordinator will communicate the participant's group assignment to the intervention research personnel, who will proceed with managing the participant's treatment according to their allocated group. The research coordinator must also complete an emergency unblinding record promptly, documenting the reason for the unblinding and any relevant details associated with the event. This record will be maintained as part of the study's documentation.

### Interventions

The standard intervention consists of two sessions of tDCS and four sessions of fNIRS. The intervention timeline is depicted in Figure 2. The tDCS sessions will be administered on the day of surgery: the first session will be conducted preoperatively and the second session will take place postoperatively in the PACU. The fNIRS assessments will be performed as part of the monitoring protocol at four designated time points throughout the study.

**Figure 2 F2:**

Timeline of the experimental design. tDCS, transcranial direct current stimulation; fNIRS, functional near-infrared spectroscopy.

The tDCS procedure is administered using a transcranial direct current stimulator, with two electrodes placed in physiological saline soaked sponges. The electrodes are secured with a stretchable cap, positioning the anode over the left dorsolateral prefrontal cortex (DLPFC) and the cathode over the right supraorbital area. The active-tDCS group will receive a 15-second ramp up phase at the start, 2 mA of tDCS for 20 min and a 15-second ramp down phase at the end. The sham-tDCS group will only receive the 15-second ramp up phase at the beginning and the 15-sencond ramp down phase at the end of each session, without the continuous 2 mA current for 20 min (6). Research personnel administering the intervention will closely monitor participants for any discomfort. If a participant experiences any intolerable discomfort, the stimulation will be immediately terminated.

Four fNIRS procedures will be conducted in relation to the tDCS interventions: (1) f_1_ (pre first tDCS) will be conducted before the first tDCS session; (2) f_2_ (post first tDCS, pre-surgery) will be conducted after the first tDCS session and before surgery; (3) f_3_ (post-surgery, before second tDCS) will be conducted after surgery and before the second tDCS session; (4) f_4_ (post second tDCS) will be conducted after the second tDCS session. The fNIRS device used is the NirSmartII-6000 A, a 41-channel system that includes 19 light emitting source probes and 16 detector probes. The system comprises near infrared light sources and avalanche photodiodes as detectors, with a sampling frequency of 11 Hz. This system continuously measures and records changes in the concentrations of oxygenated hemoglobin (HbO) and deoxygenated hemoglobin (HbR) in the brain during task performance. Relative concentration changes in HbO, HbR, and total hemoglobin (HbT) are calculated based on the modified Beer Lambert Law.

Data collection during resting state and Verbal Fluency Task (VFT): during the resting state, the concentrations of HbO and HbR across the entire cerebral cortex are recorded. In the resting state participants are required to remain quiet, awake, and relaxed, avoiding any specific mental activities or physical movements, and lie in a supine position for 5 min. During the VFT, the concentrations of HbO and HbR in the prefrontal and temporal cerebral cortex are recorded. The VFT consists of three phases: (1) pre-task phase: participants count from 1 to 5 for 30 seconds; (2) task phase: participants are presented with three Chinese characters and are instructed to form as many words as possible using each character within 20 seconds per character; and (3) post task phase: participants again count from 1 to 5 for 70 seconds. The VFT is administered via computer, and participants are instructed to remain as quiet and undisturbed as possible throughout the task.

Throughout the intervention, standard anesthesia monitoring is maintained, including non-invasive blood pressure measurement, electrocardiogram, and pulse oximetry to ensure participant safety. The administering physicians and research personnel are trained to recognize and respond promptly to any adverse events. All equipment is calibrated and maintained according to manufacturer specifications to ensure accurate and reliable data collection. Data from participants who are unable to receive both tDCS sessions for any reason will still be included in the intention to treat analysis to preserve the randomization benefits and provide an unbiased estimate of the intervention effect.

### Anesthesia procedures

Upon entering the operating room, an intravenous access is established, and routine oxygen supplementation is provided via nasal cannula. Standard anesthetic monitoring procedures are implemented, including non-invasive blood pressure monitoring, electrocardiogram monitoring, and pulse oximetry. Prior to positioning, 5 μg/kg of alfentanil are administered intravenously to alleviate pain associated with positional changes. The patient is positioned with the affected side facing upwards, and 3 ml of 2% lidocaine hydrochloride is used for local infiltration at the puncture site. Puncture is performed at the L2/3 or L3/4 intervertebral space, with clear cerebrospinal fluid observed upon puncture. Following this, 20 mg of ropivacaine hydrochloride is injected, with aspiration before and after injection to confirm the correct placement. Five min after the injection, light touch sensation is tested to assess the anesthetic level, which should reach the T10 dermatome. After confirming proper anesthesia, sterile draping is applied, and the surgical procedure is initiated.

If the surgical duration is prolonged and the patient exhibits signs of nervousness or discomfort, a small dose of etomidate lipid emulsion injection may be administered for short-term maintenance to ensure patient comfort during the procedure. Alternatively, other sedative medications may be used at the discretion of the attending anesthesiologist. Vasoactive agents are administered to maintain blood pressure and heart rate within ±20% of baseline values. Additionally, appropriate warming measures are implemented to prevent hypothermia. Postoperatively, patient-controlled analgesia (PCA) is administered using sufentanil 1.5 μg/kg and palonosetron 0.25 mg diluted in 100 ml of saline. The PCA pump is configured with a continuous infusion rate of 2 ml/h, a bolus dose of 0.5 ml, and a lockout interval of 15 min (6).

### Data collection

#### Baseline characteristics

After enrollment, the following baseline characteristics will be recorded for each subject: age, gender, height, body mass index (BMI), years of education, and preoperative comorbidities including hypertension, coronary heart disease (with a documented history), arrhythmia (defined as sinus bradycardia, sinus arrest, atrial fibrillation, and other arrhythmias requiring medication intervention), history of stroke (including ischemic stroke and hemorrhagic stroke), obesity (defined as BMI ≥ 30 kg/m^2^), Charlson comorbidity index, ASA classification, MMSE score, frailty screening scale, anxiety and depression scores, anesthesia and surgical history. Preoperative laboratory tests will include serum albumin, hemoglobin, C-reactive protein, neutrophils/lymphocytes, and type of surgery (hip replacement, open reduction and internal fixation, or closed reduction).

#### Intraoperative data

Duration of the surgery (defined as from skin incision to skin closure), duration of anesthesia (defined as from the start of monitoring after entering the operating room to the cessation of monitoring), whether nerve block is administered, total amount of anesthetic drugs used, including sedatives, dexamethasone, and vasopressor usage. volume of crystalloid and colloid fluids used during surgery, estimated blood loss, and intraoperative blood transfusion.

#### PACU

In the PACU, the intervention will be provided, and vital signs will be observed and recorded. Possible adverse reactions, such as skin tingling, mild fatigue, itching, burning sensation, skin erythema, and mild headache, will also be documented (14, 15). The fNIRS data will be processed and analyzed using the Nir Spark software package v1.7.3 (16). Initially, the raw data will be converted into optical density signals, and motion artifacts will be corrected using a three-sample interpolation method. Subsequently, the obtained signals will undergo bandpass filtering (0.01–0.2 Hz) to eliminate physiological noise from pulsation, respiration, and other sources of physiological fluctuations. For the brain activation analysis of during the VFT paradigm, a General Linear Model (GLM) will be employed to analyze the time series data of HbO and HbR. A *t* test will be conducted on the baseline and task state signals for each channel of each participant. A typical Hemodynamic Response Function (HRF) with temporal and dispersion derivatives will be selected as the fundamental function for the GLM. By calculating the degree of match between the experimental HRF values and the design values, the GLM will generate an activation coefficient (β value) representing the intensity of task induced cortical activation in the participants' brains. For HbO signals, a positive β value indicates an increase in task related cortical activation, while a negative β value indicates a decrease. For brain network analysis of resting state paradigm, Pearson correlation analysis will be performed on the time series of each pair of channels. For each participant, A 41 × 41 correlation matrix will be generated for each participant to explore the correlation between cortical activity and behavioral performance.

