### Clinical outcomes and assessments

The primary outcome of this study is the occurrence rate of delirium on post-operative days 1, 2, and 3. Secondary outcomes include the severity of POD, pain scores at rest and during movement, anxiety and depression scores, sleep quality, as well as post-operative cognitive function and complications. Another key outcome is the change of whole brain cortical networks and brain activation patterns during resting state and verbal fluency tasks.

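### The 0.01 Hz high-pass removes most of the expected verbal fluency response from a single 160 s run, and the per-channel t test within a participant has only autocorrelated samples as replicates

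*Protocol article*

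**What the plan says.** *Interventions* describes an fNIRS system "with a sampling frequency of 11 Hz". It sets out the VFT as one run: 30 s of counting, three characters at 20 s each, and then "participants again count from 1 to 5 for 70 seconds". No repetition of the task block within a run is described.

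*Data collection, PACU* says that "the obtained signals will undergo bandpass filtering (0.01–0.2 Hz) to eliminate physiological noise". This step precedes both the task analysis and the resting-state analysis, and one setting serves both. For the VFT, "a General Linear Model (GLM) will be employed to analyze the time series data of HbO and HbR", and its result is described as follows: "the GLM will generate an activation coefficient (β value) representing the intensity of task induced cortical activation in the participants' brains". The section also plans a significance test within participants, in these words: "test will be conducted on the baseline and task state signals for each channel of each participant". The test named is a t test. Nothing is said about serial correlation, or about whether the design matrix passes through the same filter.

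*Clinical outcomes and assessments* gives these data some standing: "Another key outcome is the change of whole brain cortical networks and brain activation patterns during resting state and verbal fluency tasks". *Statistical analysis* treats p-values outside the primary outcome as nominal and descriptive.

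**The concern.** Two stated choices do not fit the stated task.

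First, a high-pass at 0.01 Hz removes fluctuations slower than one cycle per 100 s. A task that appears once in 160 s carries most of its signal in a slower cycle than that. The filter would then take out much of what the GLM is meant to estimate. β is the planned measure of task activation, and it carries the VFT part of the trial's second aim, which is how tDCS acts on the brain.

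Second, with one baseline period and one task block per run, a t test within one participant and one channel has nothing to replicate over except time points. After low-pass filtering at 0.2 Hz, samples taken 11 times a second are nearly copies of their neighbours. An ordinary t test would count them as separate information and label channels activated far too often.

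**Working it through.** The article gives no power or error rate for fNIRS, so there is no fNIRS figure of its own to reproduce.

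**Inputs** (Interventions; Data collection, PACU): phases of 30 s, 3 × 20 = 60 s and 70 s; sampling at 11 Hz; pass band 0.01–0.2 Hz. **Assumptions**, because the article does not state them: a canonical double-gamma response; Butterworth filters of order 1 to 4, run forwards and backwards (zero-phase).

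**1. Task frequency against cut-off.** Run length: 30 + 60 + 70 = 160 s. Fundamental: 1/160 = 0.00625 Hz. Cut-off: 0.01 Hz, a period of 1/0.01 = 100 s. The fundamental is below the cut-off; the next harmonic, 2/160 = 0.0125 Hz, is just above it.

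**2. Share of the response below 0.01 Hz.** For a 60 s block in 160 s the duty cycle is d = 60/160 = 0.375. The fundamental's share of the variance is 2[sin(πd)/π]² / [d(1−d)] = 0.173/0.234 = 0.74. A numerical Fourier transform gives 0.67–0.74 for the block and 0.68–0.75 after convolution with the haemodynamic response, depending on zero-padding.

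**3. Effect of the filter.** With x the expected response and Fx its filtered form, the variance kept is |Fx|²/|x|². With an unfiltered design, β is multiplied by (x·Fx)/(x·x).

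| Order (zero-phase) | Variance kept | β multiplier, design unfiltered |
|---|---|---|
| 1 | 0.218 | 0.394 |
| 2 | 0.209 | 0.328 |
| 3 | 0.203 | 0.302 |
| 4 | 0.188 | 0.275 |

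The unconvolved block gives 0.19–0.21 and 0.27–0.39. A brick-wall filter gives 0.25 for both quantities. Causal filters keep 0.25–0.40 of the variance. Embedding the run in a longer recording hardly changes the zero-phase results. If the design is filtered identically, the multiplier is 1, but the removed variance is not recovered.

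**4. Net sensitivity.** The filter also removes noise. The comparison is β divided by its standard deviation, under the band-pass and under a 0.2 Hz low-pass with a linear drift term.

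- White noise: a loss of about 80% when only the 160 s record is filtered. Repeating this with 300 s of recording on either side and a filtered design gave 37–48%, so part of the larger figure is an edge effect.
- 1/f noise: a loss of about 10–40%, ranging from almost none to 47% with filter order, edge handling and whether the design is filtered.
- 1/f² drift: a gain, roughly 20–65%.

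**5. The within-participant t test.** Samples: 30 × 11 = 330 baseline and 60 × 11 = 660 task. As a rough guide, a signal confined to a band of 0.19 Hz has about 2 × 0.19 × T independent values: 11.4 in 30 s and 22.8 in 60 s. The naive standard error is then too small by about √(660/22.8) = 5.4. Since 1.96/5.4 = 0.36, the rejection rate would be near 2[1 − Φ(0.36)] = 0.72.

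Simulated pure noise with the stated filter (2,000 runs) has a lag-1 autocorrelation of about 0.998. It rejects in 61–65% of runs at the 0.05 level with white input, or 59–70% across filter orders 1 to 4. With autoregressive input (time constant 2–10 s) the rate is 71–83%. An ordinary least-squares GLM without pre-whitening rejects in 72%.

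**6. One β per participant.** Comparing 80 with 80 participants on β under the null rejected in 3% of 300 runs, consistent with 5%.

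**The case against.** **On the filter.** Filter type, order and handling of the design matrix are software settings that an article normally omits. The shrinkage to 27–39% needs an unfiltered design, which the article does not state. A reader might infer that β loses most of its usable information. Step 4 does not support that in general: the loss may be modest with 1/f noise, and steep drift turns it into a gain. Attenuation applies to both arms alike, so it costs sensitivity without favouring either arm. All of this stands. It does not remove the mismatch between a stated cut-off and a stated task, because every filter tried keeps 40% or less of the response variance.

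**On the t test.** The article never says that samples are treated as independent. The sentence sits among the GLM sentences and may mean the model's own contrast, and pre-whitening is neither stated nor excluded. That is fair, but a GLM contrast without pre-whitening has the same problem. A reader might also infer that the randomised comparison would be swamped by false positives. It would not: the plan already yields one β per participant and channel, and step 6 shows that comparing those is sound.

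**On multiplicity and pairing.** A reader might want to add that 41 channels and 41 × 40/2 = 820 channel pairs go untested for multiplicity, and that the pre/post pairing is ignored. The article does not support either as a defect. Non-primary p-values are declared descriptive. No section says that the 820 pairs are tested between arms. The VFT covers only prefrontal and temporal cortex, so 41 is an upper bound there. The outcome is defined as change, and such detail commonly sits in the analysis plan.

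**Conclusion.** The point holds in two limited parts.

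The 0.01 Hz cut-off does not suit a single 160 s VFT run. About 80% of the expected response variance is removed under zero-phase Butterworth filters of order 1 to 4, and β falls to about 27–39% of its true size if the design is left unfiltered. These figures assume a canonical response. The net loss of sensitivity rests on an unknown noise spectrum and could be small under strong slow drift.

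The t test within participant and channel is invalid as evidence of activation unless serial correlation is handled. With white input noise it rejects about 60–65% of the time under the null, and more often with smoother noise. Calling the p-values descriptive does not repair a test with that error rate.

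Neither part biases the comparison between arms, and the primary delirium analysis is untouched. The wording should be corrected before the fNIRS data are analysed.

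**What to change.** For the VFT, replace the 0.01 Hz high-pass with low-order drift terms in the GLM, or with a cut-off well below 0.006 Hz. At the least, state that the design matrix is filtered identically, which removes the shrinkage of β but does not restore the lost signal. Keep 0.01 Hz for the resting state.

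Drop the sample-level t test as evidence of activation. Carry one β per channel per participant into the arm comparison, with f2 adjusted for f1 and f4 adjusted for f3. Control of the false discovery rate over channels and pairs is optional.

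The cost is a change of wording and of processing settings, with no new data. The downsides are a little more slow drift to model in the VFT and fewer channels labelled as activated.

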### Follow-up

Delirium will be assessed during the first three post-operative days, along with pain at rest and during movement and the dosage of analgesics. On the fifth post-operative day, assessments will include the MMSE and the occurrence of any complications. The primary endpoint of the study is the completion of cognitive evaluation on postoperative day five. Delirium will be assessed by trained specialists, who will undergo a rigorous training and receive comprehensive guidance from expert psychiatric consultants prior to the commencement of the trial. Delirium will be evaluated twice daily during the first three post-operative days. The assessment time points will be scheduled from 9:00 AM to 11:00 AM and 3:00 PM to 5:00 PM, ensuring a minimum interval of 6 h between assessments. POD will be assessed using a 3-min diagnostic interview (3D-CAM) conducted by researchers who were blinded to the study group allocation. The Confusion Assessment Method (CAM) assessment is based on the four key features of delirium: acute onset and fluctuating course, disorganized thinking, inattention, and altered levels of consciousness. Investigators will also consult the medical record or contact a family member, friend, or health care provider who knows the patient well to gather additional information regarding the patient's symptoms. If POD is identified, daily assessments will continue until symptoms resolve or the patient is discharged. Delirium subtypes will be assessed using the Richmond Agitation Sedation Scale (RASS) (17). Hyperactive delirium is characterized by symptoms ranging from mild restlessness to persistent motor activity and irritability. Conversely, hypoactive delirium is characterized by one or more of the following features: reduced or absent movement, minimal verbal communication despite stimulation, and a lack of responsiveness. Mixed delirium is characterized by rapid fluctuations between the hyperactive and hypoactive states. The severity of delirium will be assessed using the Delirium Rating Scale Revised-98 (DRS-R-98) (18).

Pain at rest and during movement will be assessed using the Numeric Rating Scale (NRS) (19), an 11-point scale where 0 denotes no pain and 10 represents the worst possible pain. Anxiety will be evaluated using the Generalized Anxiety Disorder-7 (GAD-7) (20). The total score, ranging from 0 to 21, is calculated by summing up the individual item scores. A total score of 10 or higher is considered a positive result. Conversely, a score below 10 is regarded as a negative result. Depression severity will be assessed using the Patient Health Questionnaire-9 (PHQ-9) (21). Scores ranging from 0 to 4 indicate of normalcy, while scores between 5 and 9, and 10 to 14, suggest mild and moderate depression, respectively. Scores between 15 and 19, and 20 to 27, indicate moderately severe and severe depression, respectively. The Pittsburgh Sleep Quality Index (PSQI) is used to evaluate sleep quality, with scores ranging from 0 to 21. Higher scores suggest poorer sleep quality (22). The MMSE is a well-established, standardized, simple and convenient tool for cognitive screening and assessment (23). The examination encompasses six key domains: orientation, attention, calculation, memory, language, and visuospatial ability.

### Data quality and management

After screening and enrollment, participants' names will be replaced with unique four-letter codes to ensure privacy protection. Paper based data will be recorded in Case Report Forms (CRFs), which will include demographic information, medical data, intraoperative management details, post-operative follow-up data, and adverse event documentation. All collected data will be securely stored in Department of Anesthesiology, Shanxi Bethune Hospital.

### Clinical outcomes and assessments

The primary outcome of this study is the occurrence rate of delirium on post-operative days 1, 2, and 3. Secondary outcomes include the severity of POD, pain scores at rest and during movement, anxiety and depression scores, sleep quality, as well as post-operative cognitive function and complications. Another key outcome is the change of whole brain cortical networks and brain activation patterns during resting state and verbal fluency tasks.

